## Abstract

**Background:**

Dementia has a huge physical, psychological, social and economic impact upon caregivers, families and societies at large. There has been a growing impetus to utilize Internet interventions given the potential scalability, and presumed cost-effectiveness and accessibility. In this paper, we describe the design of a randomized controlled trial (RCT) aiming to study the impact of online self-help programs on caregivers of people with dementia in India. The experimental group will receive an interactive training and support program and the comparison group will receive an education-only e-book. It will be among the first online support intervention RCTs for a mental health condition in a lower-middle income country.

**Methods and design:**

Two hundred and eight participants are expected to be recruited via several strategies (email, Internet and social media, telephone and face-to-face) starting in the Bangalore region of India. The inclusion criteria for participation in the trial are: (1) being 18 years or older, (2) being a self-reported caregiver of a person with dementia, (3) self-report that a family member has a diagnosis of dementia (AD8 ≥ 2), and experience caregiver distress (≥ 4 on a 1-item burden scale ranging from 1 to 10 *or* ≥ 4 or < 20 on the Center for Epidemiologic Study-Depression (CES-D) scale (10-item) or ≥ 4 or < 15 on the Generalized Anxiety Disorder Scale (7-item).

The intervention group will be offered iSupport, an online self-help training and support program, enabling a personalized education plan with a maximum of 23 lessons. These modules present a range of topics from “what is dementia?” to “dealing with challenging behaviors like aggression.” The comparison group will receive an education-only e-book containing similar content. The outcomes of this trial are: caregiver burden as measured by the 22-item Zarit Burden Scale, depressive symptoms, anxiety symptoms (primary outcomes), quality of life, person-centered attitude, self-efficacy and mastery (secondary outcomes).

**Discussion:**

Based on the findings of this trial, we will examine the potential use and scale up of iSupport for caregiver distress in India. This style of online self-help programs could be expanded to other regions or countries or to other suitable caregiver groups.

**Trial registration:**

Clinical Trials Registry—India (CTRI), ID: CTRI/2017/02/007876.

**Electronic supplementary material:**

The online version of this article (10.1186/s13063-018-2604-9) contains supplementary material, which is available to authorized users.

## Background

Dementia is a global public health priority since the disease has a huge impact on caregivers, family and society in physical, psychological, social and economic terms [1, 2]. Currently, there are 47.5 million people with dementia worldwide, a number that is due to triple by 2050 [2, 3]. Most people with dementia are cared for by family or other unpaid and untrained caregivers without any additional support, especially in lower-middle income countries [2, 4]. These caregivers often face numerous stressors, such as time pressures, changed behaviors and financial stress which can be challenging for them to cope with and balance with demands from work and family [2]. These stressors often lead to significant health problems such as depression, anxiety and physical problems for caregivers themselves [5, 6].

Research, mostly carried out in high-income countries, shows that training and support might help reduce psychological distress in caregivers of people with dementia. For example, support groups for caregivers of people with dementia have a beneficial impact on diverse caregiver outcomes, including feelings of burden, mental health, depressive symptoms, and, for example, the quality of the relationship with the person with dementia, for women in particular [7]. In these support groups, caregivers share their experiences of caring; learning about dementia and its impact on daily life. They learn about available resources and are trained to better cope with the person with dementia and the care situation.

A large body of evidence, also mostly carried out in high-income countries, shows that multicomponent interventions have a beneficial impact on caregivers of people with dementia. Some multicomponent interventions are customized and tailored to the specific situation of the caregivers and their needs [8–10]. They include, for example, skills training for caregivers, psycho-education, planning pleasant activities, changes in the environment, increasing social support, teaching techniques to better care for themselves, physical training, home care and case management [5, 10–13].

In the last decade, there has been a growing interest in the use of information and communications technologies and the Internet for people with dementia and their caregivers, including online training and support programs [14]. One line of research has been to create caregiver interventions specifically for Internet delivery. A potential reason is scalability, which is important and urgent because of the demographic changes. Internet-based approaches are also attractive because caregivers can access the program at a convenient time in the privacy of their own home. They do not have to travel to a clinic or physician appointment which may induce stigma, because they often do not consider themselves as the ones who need care, and it does not require arranging alternate care for their family member, or transportation [15].

A few trials in high-income countries showed promising results of Internet-based training and support programs for caregivers of people with dementia, with a reduction of caregiver depressive symptoms, anxiety symptoms and perceived stress, although the full potential of these programs has not been reached yet [16–19].

Though one often thinks of caregiver distress in high-income country contexts, but it is, in fact, an even larger issue for lower-middle income countries, like India [20, 21]. There are only a few formal skilled nursing facilities, retirement homes and other residential care options for older people in India [22, 23]. Most people with dementia (at least 95%) are cared for at home by their family only [4, 24, 25]. The need for training and support services for people with dementia and their caregivers far outpace the health and social services and personnel that exist. As the population of India (over 1.3 billion) ages, this will be a growing problem.

Using Internet-based methods for caregiver training and support may also be promising in lower-middle income countries, in countries with a high number of Internet users like India. The number of Internet users in India is estimated at more than 460 million and Internet penetration is rapidly increasing [26].

The development of training and support for caregivers is emphasized as a strategic priority in the World Health Organization (WHO) action plan on dementia and on aging and health, both approved by the WHO’s 194 member states. This is especially the case for lower-middle income countries such as India [21, 27]. Therefore, the WHO has brought together a panel of international experts to develop “iSupport,” a self-help online training and support program aimed at relieving caregivers’ psychological distress.

In this article, we describe the design of an RCT in India to examine the effectiveness of iSupport.

## Methods and analyses

The trial design is a two-group RCT to establish the effectiveness of an online self-help training and support program (iSupport) compared to an education-only comparison condition (EOC) which provides education about dementia and caregiving through an on-line e-book (Fig. 1). The objective is to examine the effect of this online self-help training and support program on depression and anxiety outcomes. The RCT will last 6 months in total, including pre measurement (T0), first follow up (T1, 3 months after T0) and second follow-up (T2, 3 months after T1). The timeline of assessments and measures are described in Fig. 2.

**Fig. 1 Fig1:**
[figure not shown]
Flowchart of the iSupport Online Self-Help Program. T0 pre-measurement, T1 = first follow up 1–3 months post baseline, T2 second follow up: 2–6 months post T0

**Fig. 2 Fig2:**
[figure not shown]
SPIRIT Flowchart of the iSupport online self-help program

This trial is set in India, a lower-middle income country with a rapidly aging population and a high number of Internet users. National Institute for Mental Health and Neuro Sciences (NIMHANS), one of the premier institutes that provide neuropsychiatric services to older people in India, is executing the trial.

### Ethical approval

The study was approved by the Medical Ethics Committees of the World Health Organization (WHO) and the National Institute of Mental Health and Neurosciences (NIMHANS). The trial was registered at the Clinical Trials Registry—India (CTRI), protocol # CTRI/2017/02/007876.

### Recruitment

Participants are recruited using several strategies: social media outreach, telephone calls and face-to-face contact. On social media (Facebook, WhatsApp and Twitter), regular posts including a short video, electronic flyers and messages are posted to targeted groups that may have an interest in online training and support. In addition, email flyers are sent to NIMHANS staff, community-based organizations serving older people, and employees at information technology companies in the local Bangalore area (with permission). On-going publicity appears in Bangalore print media. Person-to-person recruitment strategies include the posting of flyers at NIMHANS; for example, in the waiting areas of specific clinics for people with dementia. In addition, family caregivers of people with dementia who are already in the NIMHANS or some other care systems involved in the recruitment for this study are personally invited to participate in the study. Beyond Bangalore, recruitment efforts are primarily through Alzheimer’s and Related Disorders Society of India (ARDSI) with chapters in 20 large cities throughout India and some specialists who are involved in the health care for people with dementia.

### Inclusion criteria

Participants are screened online to assess whether they are (1) aged 18 years and older, (2) are a self-reported caregiver of a person with dementia, (3) self-report that their family member has a diagnosis of Alzheimer’s disease or dementia (score ≥ 2 on the AD8) [28]. In addition, the caregiver should reside in India and have access to the Internet. For inclusion, the caregiver should experience some psychological distress, as indicated by some subjective burden (defined by a score of ≥ 4 on a 1-item burden scale ranging from 1 to 10) [29] or some symptoms of depression or anxiety (score ≥ 4 and < 15 on the Generalized Anxiety Disorder (GAD) Scale (7 items) [30] or ≥ 4 and < 20 on the Center for Epidemiologic Study-Depression (CES-D) scale (10 item) [31, 32]. If potential participants have a score of 20 or higher on the 10-item CES-D, and ≥ 15 on the GAD, caregivers are referred to the mental health services at NIMHANS or providers in their region. As this is an online intervention, and participants may be from all over India, no further referral or follow-up are given.

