### Randomization

After screening, participants who fulfil the inclusion criteria are requested to provide informed consent to enrol in the study. Next, they are asked to fill out the questionnaires at baseline, after which randomization is carried out using an automated computer-generated random number allocation, stratified by sex and relationship to the care recipient (spouse/other) with a block size of 2. Participants are masked to their intervention status.

To randomize the participants, a table is filled with “real random” 0 or 1 codes preceding the start of the project, drawn with equal probability (50%) from the Random.org site [33]. This table is subsequently linked to the table with the accumulation of participant data. Immediately before randomization, the questionnaire script determines what block-condition (male/female; spouse/no spouse) applies to the participant. Next, with a block size of 2, there are two options:If a new block must be opened for the new participant: the participant’s condition will be determined by the “real random” value in the linked table. Thus, if the random value is 0, the participant’s condition will be 0 and if the random value is 1, the condition will be 1If a block is already open and partially filled (thus, with a block size of 2, with one other respondent), the new participant’s condition will be the other condition of the first participant. So, if the first participant has condition 0, the new participant’s condition will be 1, etc.

Baseline characteristics of individuals randomized to either of the two conditions will be compared to ensure that randomization was successful. If an individual that is enrolled in the trial drops out after enrollment, is lost to follow-up or discontinued from the study, their data will be analyzed using the intention-to-treat principle.

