### Covariates

Several other variables are measured, such as the age of the caregiver, their sex, their relationship to the person with dementia (spouse, adult child, or other family member), level of education of the caregiver, living arrangement (living together or apart from the person with dementia).

All study data will be collected within the iSupport online tool using encryption for participant protection. Data are securely stored using a cloud-based encrypted platform. Data will only be accessed by project team members involved in data analyses. Confidentiality will be maintained before, during and after the trial. Study participants who discontinue use of the tool will be sent automatic weekly reminders to promote adherence. There is no external data monitoring board. The study team will take appropriate action in case any adverse effects are reported.

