## Discussion

Dementia is a global public health priority. Especially in lower-resourced settings, a huge gap exists whereby there are not enough care providers and yet, there is a rapidly growing rate of dementia. Given this, risk reduction of dementia is important, as is the training and support for family and other caregivers to provide care to people who already have dementia or will have dementia. Family caregivers face significant challenges when providing care to people with dementia, putting them at greater risk for severe health problems, such as depression, anxiety and functional decline [27, 34, 42, 43].

In this RCT, we study the effectiveness of iSupport, an online training and support program. It is among the first of its kind adapted for a lower-resourced setting, delivered without the intervention of a health care professional, easily accessible via the Internet. In this trial, caregivers who use iSupport are compared to those who receive education only using the following outcomes: burden, and symptoms of depression and anxiety (primary outcomes); quality of life, person-centeredness, self-efficacy and mastery (secondary outcomes). The outcomes chosen for this trial have been used in several other trials related to Internet support and caregiver distress, internationally [14, 16–18].

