## Trial status

The trial has completed initial planning and pilot testing. The trial is currently enrolling participants.

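### As written, a caregiver above only one of the two symptom cut-offs is not referred and may still be enrolled

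*Protocol article*

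**What the plan says.** All of the relevant rules are in the protocol article.

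- **Entry (Inclusion criteria).** "For inclusion, the caregiver should experience some psychological distress, as indicated by some subjective burden" of at least 4 on a single 1–10 item, *or* by GAD-7 from 4 to 14, *or* by CES-D10 from 4 to 19. The upper limits belong to the two symptom alternatives. The burden alternative has none.
- **Referral (same section).** "If potential participants have a score of 20 or higher on the 10-item CES-D, and" 15 or higher "on the GAD, caregivers are referred to the mental health services at NIMHANS or providers in their region". The section then says that, because the programme is online and nationwide, nothing beyond this referral is provided.
- **What follows screening (Randomization).** "participants who fulfil the inclusion criteria are requested to provide informed consent to enrol in the study". The baseline questionnaires follow consent, and randomization comes after that. No separate exclusion for high scores is stated.
- **Setting.** The Discussion describes the programme as "delivered without the intervention of a health care professional". The Covariates section says there is no external data monitoring board and that "The study team will take appropriate action in case any adverse effects are reported". Trial status says "The trial is currently enrolling participants".
- **Scale ranges (Table 1).** CES-D10 runs from 0 to 30 and GAD-7 from 0 to 21.

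**The concern.** The referral cut-offs are the exact complements of the entry limits: 20 and above against below 20 on the CES-D10, 15 and above against below 15 on the GAD-7. That pattern suggests a rule meant to work scale by scale. The sentence joins the two cut-offs with *and*, so a caregiver with a very high depression score and a moderate anxiety score, or the reverse, does not trigger it.

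Screening is done online, so the sentence could be turned directly into code. A caregiver missed at that step has no second chance in the text: no later referral or follow-up is described, no health professional takes part in delivery, and the stated safeguard waits for an adverse effect to be reported. At stake is whether highly distressed caregivers are directed to care and, secondarily, which of them enter the trial.

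**Working it through.** The plan gives no figure to reproduce. The check applies the written rules to scores.

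**Rules**

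- Literal entry: burden ≥ 4, or 4 ≤ GAD-7 < 15, or 4 ≤ CES-D10 < 20.
- Stricter entry, if the limits were meant to exclude by any route: the literal rule, and also CES-D10 < 20 and GAD-7 < 15.
- Referral as written: CES-D10 ≥ 20 and GAD-7 ≥ 15.
- Referral per scale: CES-D10 ≥ 20 or GAD-7 ≥ 15.

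**Example profiles**

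| Burden | CES-D10 | GAD-7 | Literal entry | Stricter entry | Referred, *and* | Referred, *or* |
|---|---|---|---|---|---|---|
| 6 | 28 | 10 | yes (burden, GAD-7) | no | no | yes |
| 2 | 28 | 10 | yes (GAD-7) | no | no | yes |
| 2 | 28 | 2 | no | no | no | yes |
| 6 | 10 | 18 | yes (burden, CES-D10) | no | no | yes |
| 2 | 10 | 18 | yes (CES-D10) | no | no | yes |
| 2 | 2 | 18 | no | no | no | yes |
| 6 | 24 | 17 | yes (burden) | no | yes | yes |
| 2 | 24 | 17 | no | no | yes | yes |
| 6 | 12 | 8 | yes | yes | no | no |

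The first six rows are high on one scale only. None is referred under *and*; all are referred under *or*. Four of the six meet the literal entry rule and two do not. Under the stricter rule all six are turned away, still unreferred. The referral gap therefore does not depend on how the entry limits are read.

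**All score combinations**

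Burden takes 10 values, GAD-7 22 and CES-D10 31, so there are 10 × 22 × 31 = 6,820 combinations. At or above the cut-off lie 11 CES-D10 values (20–30) and 7 GAD-7 values (15–21); below it lie 20 and 15.

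- Above both: 10 × 11 × 7 = 770.
- Above exactly one: 10 × 11 × 15 + 10 × 20 × 7 = 1,650 + 1,400 = 3,050.
- Referred as written: 770. Referred per scale: 770 + 3,050 = 3,820.

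The 3,050 combinations above exactly one cut-off divide as follows under literal entry:

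- Burden ≥ 4 (7 of 10 values): 3,050 × 7/10 = 2,135 eligible.
- Burden 1–3, other symptom scale in range: 3 × 11 × 11 + 3 × 16 × 7 = 363 + 336 = 699 eligible.
- Burden 1–3, other symptom scale below 4: 3 × 11 × 4 + 3 × 4 × 7 = 132 + 84 = 216 not eligible.

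Eligible and unreferred: 2,135 + 699 = 2,834. Neither eligible nor referred: 216. The combinations are not equally likely, so these counts show which scores the rule misses and do not estimate the proportion of caregivers missed.

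**The case against.** The best reply is that this is loose wording and the rule itself is sound. The cut-offs mirror the entry limits, and the sentence can be read distributively: those high on one scale, and those high on the other, are referred. Connectors are loose elsewhere too. The Abstract joins each lower and upper bound with *or*, which read literally bounds nothing. A full protocol and a correctly coded screener may exist, and two ethics committees approved the study. Much of this stands. A per-scale rule was probably meant, and if the screener already applies it only the text needs correcting. But the article states a rule, and the rule as stated is the wrong one. Nothing else in the article corrects it.

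A reader might infer that the entry rule is contradictory. It is not: read literally it is determinate, and being eligible and being referred are compatible. The uncapped burden route is also coherent, since burden is the outcome behind the sample size. What is left is a request to say whether the limits were meant to exclude.

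A reader might also place the gap only among caregivers with burden of 4 or more. The 699 combinations that enter through the other symptom scale show that this is too narrow.

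**Conclusion.** The point holds. As written, no caregiver above exactly one cut-off is referred, under either reading of the entry limits. Under the literal entry rule such a caregiver can be enrolled through burden or through the other symptom scale, which covers 2,834 of the 3,050 combinations concerned.

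This rests on taking the printed *and* at face value. How many caregivers it touches cannot be known, because the article gives no score distribution and does not show the live screener. Since enrolment is under way, a reader might infer that distressed caregivers have already been missed; the document does not support that, and it is a reason to check. Nor does the point extend to the validity of the comparison: screening precedes randomization and applies to both arms alike, so alpha, power and between-arm bias are unaffected. It is a participant-safety correction that the sponsor should make.

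**What to change.** 1. Change the trigger to: refer if CES-D10 ≥ 20 **or** GAD-7 ≥ 15.
2. Check that the online screener applies this rule, and correct it if not.
3. Send the same referral information to anyone already screened above either cut-off, where scores and contact permissions allow. Enrolled participants have both scales recorded at baseline (Table 1). People screened but not enrolled did not reach the consent step, so contact may not be possible.
4. As a secondary clarification, state whether a score at or above either cut-off excludes by any route, or whether such caregivers may enrol and are also referred. This is for the clinical team to decide.

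The cost is a wording change, a script check and some more one-off referrals. The look-back may need an access arrangement, because the Covariates section restricts data to team members involved in the analyses. If the limits become exclusions, the eligible pool shrinks by an amount the article does not allow one to estimate.

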### Randomization

After screening, participants who fulfil the inclusion criteria are requested to provide informed consent to enrol in the study. Next, they are asked to fill out the questionnaires at baseline, after which randomization is carried out using an automated computer-generated random number allocation, stratified by sex and relationship to the care recipient (spouse/other) with a block size of 2. Participants are masked to their intervention status.

To randomize the participants, a table is filled with “real random” 0 or 1 codes preceding the start of the project, drawn with equal probability (50%) from the Random.org site [33]. This table is subsequently linked to the table with the accumulation of participant data. Immediately before randomization, the questionnaire script determines what block-condition (male/female; spouse/no spouse) applies to the participant. Next, with a block size of 2, there are two options:If a new block must be opened for the new participant: the participant’s condition will be determined by the “real random” value in the linked table. Thus, if the random value is 0, the participant’s condition will be 0 and if the random value is 1, the condition will be 1If a block is already open and partially filled (thus, with a block size of 2, with one other respondent), the new participant’s condition will be the other condition of the first participant. So, if the first participant has condition 0, the new participant’s condition will be 1, etc.

Baseline characteristics of individuals randomized to either of the two conditions will be compared to ensure that randomization was successful. If an individual that is enrolled in the trial drops out after enrollment, is lost to follow-up or discontinued from the study, their data will be analyzed using the intention-to-treat principle.

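### Fixed, published blocks of 2 make every second allocation in a stratum deducible to anyone who knows the previous one; larger, randomly varying blocks would cost almost nothing

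*Protocol article*

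**What the plan says.** The Randomization section states that allocation is "stratified by sex and relationship to the care recipient (spouse/other) with a block size of 2". Sex (two levels) by spouse/other (two levels) gives four strata.

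- **First place in a block.** The arm comes from a table of 0/1 codes "drawn with equal probability (50%) from the Random.org site".
- **Second place.** If a block is already open, "the new participant’s condition will be the other condition of the first participant".
- **Timing.** Participants are screened, consent and complete the baseline questionnaires, "after which randomization is carried out using an automated computer-generated random number allocation". The stratum is also found by the program: "Immediately before randomization, the questionnaire script determines what block-condition (male/female; spouse/no spouse) applies to the participant".
- **Masking.** "Participants are masked to their intervention status". The section does not mention masking of staff.

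Other sections bear on the point. Under Recruitment, caregivers already in contact with NIMHANS or other participating care systems "are personally invited to participate in the study", alongside social media, email, print and chapters of a national society in 20 cities. The sections on the two conditions describe an interactive program with instant feedback in one arm and an e-book without interaction in the other. The Covariates section restricts data access to project team members who work on the analyses. Trial status says enrolment is under way.

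**The concern.** Two is the smallest possible block, so it gives away the most. One known allocation, plus the knowledge that it opened a block, fixes the next allocation in that stratum. The block size and both stratification factors are public, and a recruiter can see a caregiver's sex and spouse status.

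A script keeps the table hidden, but it does not stop deduction from allocations already made. Those can become known, because the arms look different and a caregiver seen in clinic can describe what was received. A staff member with that knowledge could choose whom to invite, or when.

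The stake is selection bias in a trial designed around a standardized effect of 0.33. Burden, depression and anxiety are all measured at T0, and adjustment for confounders is planned. Adjustment can reduce imbalance on measured variables, but not on unmeasured ones.

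**Working it through.** **Inputs.** Block size 2, four strata, first place 50/50, second place fixed (Randomization section); N = 208 (Sample size calculation section). The article gives no figure for predictability, so there is none to reproduce.

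**1. Current rule, full stratum history known.**
- Certain allocations: 1 of every 2 = 50%, at most 208/2 = 104. Simulating 208 participants over four strata gives 49.5% (about 103), because some blocks stay open at the end.
- Correct guesses: (0.5 + 1)/2 = 75%.
- Equal stratum shares and assumed shares of 10/15/35/40% give the same results.

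**2. Current rule, partial knowledge.** Suppose the observer sees a random share *s* of allocations in a stratum and guesses the opposite of the last one seen. The documents give no value for *s*.
- If the last one seen is the immediate predecessor (probability *s*), the two share a block half the time: 0.5 × 1 + 0.5 × 0.5 = 0.75.
- If it lies further back, it is in another block: 0.5.
- Guess rate = 0.75*s* + 0.5(1 − *s*) = 0.5 + 0.25*s*.

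| Share seen (assumed) | Correct guesses |
|---|---|
| 0% | 50% |
| 10% | 52.5% |
| 25% | 56.25% |
| 50% | 62.5% |
| 100% | 75% |

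An observer who sees every allocation but ignores the strata guesses about 64% correctly (simulated).

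**3. Random blocks of 4 or 6 (equally likely), full stratum history known.** The observer guesses the under-represented arm. In a block of size 2m the expected number of correct guesses is m + (2^(2m)/C(2m,m) − 1)/2.
- m = 1: 1 + (4/2 − 1)/2 = 1.5 of 2 = 75%, matching step 1.
- m = 2: 2 + (16/6 − 1)/2 = 2.833 of 4.
- m = 3: 3 + (64/20 − 1)/2 = 4.1 of 6.
- Mixed: (2.833 + 4.1)/10 = 69%. Simulation also gives 69%.

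Certain allocations, if the observer knows that sizes are 4 or 6 but not the size of the current block: about 6% (simulated). If the current size were also known, the share would be about 27%, which is an upper bound.

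**4. Balance given up.**
- Blocks of 2: at most 1 per stratum, so 4 overall, or 102 v 106. Efficiency 4 × 102 × 106/208² = 0.9996.
- Blocks up to 6: at most 3 per stratum, so 12 overall, or 98 v 110. Efficiency 4 × 98 × 110/208² = 0.997.

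**The case against.** The strongest reply is that nobody in this trial is in a position to use the pattern. No person is described as assigning participants. Screening is online, and the script finds the stratum and allocates only after consent and baseline. Entry may come from anywhere in India, so a recruiter would need to know the last entrant in the stratum nationwide, and any unseen entrant spoils the prediction. Data access is restricted, and participants are masked. The 75% figure is thus a worst case, and even for an all-seeing observer the change lowers the guess rate only to 69%.

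Most of this stands. A reader might infer from the block size that allocation concealment is broken, or that every second allocation is openly predictable. The article does not support either reading: prediction needs the previous allocation and the open state of the block, and nothing shows that a recruiter has both.

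The reply does not close the route altogether. Personal invitation gives staff some influence over who enters and when. The access rule does not say that recruiters are separate from the analysis team, and it cannot prevent participants from telling staff what they received. A condensed article may leave such separation to the full protocol, so its absence is not evidence of access. The block rule itself, however, is stated and fixed here.

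**Conclusion.** The point holds in a conditional form. By the stated rule, half of all allocations follow from the one before in the same stratum. An observer with the full stratum history would guess 75% correctly; one with partial knowledge would fall between 50% and 75%. Whether any recruiter has such knowledge is neither stated nor excluded, and no breach is shown.

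The main gain from larger random blocks is in certainty (about 50% to about 6%, assuming the current block size is unknown); the fall in the guess rate is modest. The case for the change is that a small, avoidable exposure can be removed almost free of charge. It does not cast doubt on the allocations made so far.

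**What to change.** - For new blocks, change the script to permuted blocks of randomly varying size, for example 4 and 6, within the same four strata.
- Keep the new sizes out of public and site documents.
- Let open blocks of 2 close, keep all allocations already made, and record the date of the change.
- State in the protocol that staff who invite caregivers cannot see accumulating allocations.

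The cost is a small script change and a short amendment, with no extra participants. Balance becomes slightly looser, with a worst-case efficiency loss of 0.3%. The change gives no protection to allocations already made, so it is worth more the sooner it is done.
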